### Frequency and plans for auditing trial conduct {23}

The monitoring Committee is entitled to review and inspect the relevant materials of the trial and supervise the implementation process by telephone, email, or video regularly to ensure that the study is carried out according to the protocol.

### Plans for communicating important protocol amendments to relevant parties (e.g., trial participants, ethical committees) {25}

Any modifications that may have an impact on the study, potential benefit to patients, or affect patient safety, including changes of the study objective, study design, patient population, sample size, or study procedure will require a formal revision of the study protocol. This will be decided jointly with the monitoring Committee and the Clinical Research Center of Drugs and approved by the Ethics Committee.

### Dissemination plans {31a}

The publication of the outcomes of this study will provide baseline data and acupoint ultrasound images as well as acupoint ultrasound scanning practices procedure. The outcomes may be presented at conferences, symposiums, teaching classes, etc., if applicable.

## Discussion

*Deqi* refers to the patient’s experience of soreness, numbness, distention, and heaviness and the doctor’s sense of a heavy and tight sensation coming from beneath the acupuncture needle, as described vividly in Biao you fu (Odd to Elucidate Mysteries) written by DOU Han-qing in Yuan Dynasty [39], “*Qi* has not been achieved if the feeling is light, unstable and slow; on the contrary, if the feeling is heavy, sinking and tight, the qi can be achieved.” “*Arrival of qi* is just like ups and downs of the fish after swallowing the bait, non-*arrival of qi* is like the profundity of deep and serene ancient hall.” Obviously, feelings under the needle tip like “fishing bite” indicates “*arrival of qi.*” The essence of acupuncture therapy lies in regulating *qi*. *Arrival of qi* is the precondition for *deqi*; meanwhile, *deqi* is the continuation of *arrival of qi* and the premise of acupuncture manipulation [19].

The main objective of our trial is to design a robust trial to study the relationship between *deqi* sensations, the depth of needling, and the acupuncture effect of a specific point. We will overcome the safety challenges presented when an acupuncturist performs needling by observing ionizing radiation damage, as demonstrated in previous acupuncture clinical trials. In order to achieve this goal, we designed a strictly randomized controlled trial using ultrasonic imaging technology with the ability to observe and record in real time, using high-resolution probes to locate acupoints and capture the static and dynamic state of the target structure.

Assessing the *deqi* sensations is an important part of this trial. General understanding of the term *deqi* is not accurate enough to focus solely on patient’s feelings or acupuncturist’s perception as the criteria of *deqi*. Actually, *deqi* is an umbrella term for a group of phenomena, signifying a state of *qi* and blood changing in the body after being stimulated by acupuncture, moxibustion, or acupoints pressure of meridians [40]. Based on that, we will use both subject’s and acupuncturist’s clinical evaluation scales to the assess *deqi* and needling sensations. Furthermore, we will also use a medical infrared imager to measure skin temperature changes on the abdomen, considering that ST36 is the He point of the stomach meridian of foot-yangming.

The key technical problems to be solved in this experiment are as follows: (1) the measurement of thermal infrared imaging is sensitive to ambient temperatures (2) to observe and guide the whole process of needling and obtain a legible ultrasound image of the needle body and (3) the application of the sham acupuncture method. The human skin surface temperature changes very little in a constant temperature environment. So, we will use a highly sensitive and accurate thermometer to monitor the room temperature in real time, in a closed space without convection gas or other extraneous heat source. It is necessary for the needle body to be perpendicular to the acoustic waves in order for optimal propagation. Only by using this orientation can we effectively guide the whole process of the needling. This means acupuncturists will need to penetrate into the skin at a point away from the routine insertion point. Nonetheless, we can also guarantee that the acupuncture area is located with precision. The acupuncturist and sonologist should be trained several times before the trial begins to ensure an effective implementation of the sham acupuncture technique and to be prepared to give reasonable explanations in case of doubts from sham acupuncture group participants.

There are some limitations in this randomized controlled trial. It is inevitable for acupuncturists to know when they are implementing the real or sham acupuncture treatment and its possible effects. To minimize suggestive bias from this limitation, we will ask all participants to wear an eye-mask. This trial is the primary study into the effect of a specific acupoint in relation to the *deqi* condition. In further studies, we may consider a multicenter clinical trial with patients. We expect that this study will provide more credible evidence for the effect of *deqi* sensations and the specificity of ST36 on gastric antrum contraction function and make up for the deficiency of current clinical trials focused on the methodology of acupuncture.

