### Relevant concomitant care permitted or prohibited during the trial {11d}

Participants will not be allowed to eating or drinking during the entire study. In order to avoid the influence of other factors on body temperature, participants should also be prohibited from leaving the bed for free movement.

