#### Infrared thermal spectrum

The infrared thermal spectrum will be measured for 10 min before and after needling by FOTRIC 225 medical infrared imager. We will take the value of the highest temperature within 10 min as the final result of skin temperature in the abdominal region.

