## Statistical methods

### Statistical methods for primary and secondary outcomes {20a}

Data analyses will be performed with the statistical software SPSS23.0 by an independent statistician. The analysis will include an intention-to-treat(ITT) analysis, including data for all participants who dropped out of the trial. Descriptive statistical analysis will be used for all demographic and clinical characteristics of subjects such as sex, age, and weight. We will validate the homogeneity of demographic characteristics and examine the variables between the 2 groups. The mean ± standard deviation will be used for description of the continuous variables. Qualitative data will be expressed in terms of frequency and percentage.  Student's t-test will be used to compare the measurement data between the 2 groups. Rank-sum test is used for ranked data, while the chi-squared test is adopted to analyze categorical data. The significance level used for statistical analysis with 2-tailed testing will be 5%.

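### Skin temperature is compared by an unadjusted t-test, although the protocol calls room temperature a key problem and states no use for the readings: a minor loss of precision on one secondary outcome

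*Protocol article*

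**What the plan says.** The Discussion of the protocol article puts first among its key technical problems that "the measurement of thermal infrared imaging is sensitive to ambient temperatures". It starts from the premise that "The human skin surface temperature changes very little in a constant temperature environment", and responds with two measures in one sentence: "we will use a highly sensitive and accurate thermometer to monitor the room temperature in real time", and doing so "in a closed space without convection gas or other extraneous heat source". Section {11d} adds a restriction on participants: "In order to avoid the influence of other factors on body temperature, participants should also be prohibited from leaving the bed for free movement".

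The outcome is defined under Infrared thermal spectrum: "The infrared thermal spectrum will be measured for 10 min before and after needling by FOTRIC 225 medical infrared imager". The summary value is a maximum: "We will take the value of the highest temperature within 10 min as the final result of skin temperature in the abdominal region". The Abstract lists the change in this measure among the secondary outcomes, and Objectives {7} names abdominal skin temperature in both the hypothesis and the first objective.

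For the analysis, section {20a} says that Student's t-test "will be used to compare the measurement data between the 2 groups". Section {20b} states that no additional analyses are planned.

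**The concern.** Monitoring a room shows drift but does not remove it. The article gives no set point or tolerance, does not say that readings become data, and gives them no role in the analysis.

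The Acupuncture group description in {11a} shows why drift within a session is possible. The first infrared window is followed by 10 minutes of ultrasound, the needling, another 10 minutes of ultrasound and the drying of the skin, and only then by the second window. At least 20 minutes therefore separate the two, in a closed room with staff and running equipment. Any movement in room temperature over that time enters each participant's change, and a maximum over 10 minutes does not average out an upward drift.

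At stake is the width of the confidence interval for the arm difference in skin temperature. The stated t-test also makes no use of baseline skin temperature as a covariate, although it is measured in everyone who completes the first window.

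**Working it through.** **The plan's own figure.** There is none for this outcome. The 116 in Sample size {14} rests on response rates of 70% and 40% for antral contraction frequency. It reproduces with the unpooled formula: (0.7 × 0.3 + 0.4 × 0.6) × (1.960 + 1.282)² / 0.30² = 52.54 per arm, and 52.54 × 1.1 = 57.8, so 58 per arm. It does not bear on skin temperature.

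**Share of variance due to room drift.** Let s be the SD of the change in room temperature between the two windows, b the skin response per °C of room change, and e the SD of the skin-temperature change from all other sources. Then

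share = (b·s)² / [(b·s)² + e²].

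The documents give none of the three. Assumed ranges: s 0.3 to 1.0 °C, b 0.2 to 0.4 °C per °C, e 0.3 to 0.5 °C.

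| Case | s | b | e | Calculation | Share |
|---|---|---|---|---|---|
| Lowest | 0.3 | 0.2 | 0.5 | 0.0036 / 0.2536 | 1.4% |
| Central, moderate drift | 0.5 | 0.3 | 0.4 | 0.0225 / 0.1825 | 12% |
| Midpoint of all three ranges | 0.65 | 0.3 | 0.4 | 0.0380 / 0.1980 | 19% |
| Highest | 1.0 | 0.4 | 0.3 | 0.16 / 0.25 | 64% |

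As s approaches 0 the share approaches 0. In sample-size terms, a share of 12% corresponds to a factor of 0.1825 / 0.16 = 1.14, and 19% to 0.1980 / 0.16 = 1.24.

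**Effect on the standard error.** If the covariate has correlation ρ with the outcome, the standard error is multiplied by √(1 − ρ²), and ρ² is the share above. For a t-test assumed to have 80% power without adjustment:

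| ρ | SE factor | Power |
|---|---|---|
| 0.1 | 0.995 | 80.4% |
| 0.3 | 0.954 | 83.6% |
| 0.5 | 0.866 | 89.9% |
| 0.7 | 0.714 | 97.5% |

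Shares of 12% and 19% mean ρ of about 0.35 and 0.44, so power would lie between 83.6% and 89.9%. The 80% starting point is only an illustration, since the trial is not powered for this outcome.

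**Baseline skin temperature.** With equal SDs before and after and within-person correlation r, the variance of a change score is proportional to 2(1 − r), and that of the baseline-adjusted comparison to 1 − r². Their ratio is (1 + r)/2, which never exceeds 1. Apart from one degree of freedom, this adjustment cannot lose against a t-test on changes, whatever the room does. The documents do not give r, so this gain is not quantified. The shares above concern room drift alone and are not the total gain of the model proposed below.

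**The case against.** The strongest reply is that the protocol deals with ambient temperature by design. The sentence about monitoring goes on to specify a closed space without air flow or extra heat sources, and participants stay in bed. If those measures keep the room steady, little is left to adjust for. This stands: the gain from the room covariate could be negligible.

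Second, a reader might infer that recruitment from December 2020 to late 2021 adds seasonal noise. The outcome is a within-person change, so stable differences between sessions largely cancel. Only drift within a session, or a response that itself depends on room temperature, remains.

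Third, a reader might infer that the arm comparison is biased. The documents do not support that. Apart from needle depth and manipulation, section {11a} gives both arms the same procedures, and randomisation balances drift in expectation. The t-test is valid.

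Fourth, a reader might take the readings to be data already in hand. The text speaks of monitoring only. Logging is a new step, though a small one.

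Fifth, covariates for a secondary outcome are often left to the analysis plan, which is not shown. This carries some weight for the room-temperature term. It does not remove the point, because the protocol itself names the test and rules out additional analyses.

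**Conclusion.** This is a minor point, and an improvement to the plan more than the correction of an error. The protocol names a source of error, monitors it, states no use for the readings, and fixes an unadjusted test for the outcome concerned. The consequence is possible loss of precision on one secondary outcome. The primary outcome and the sample size are untouched.

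The documents do not establish the size of the loss. The range of 1% to 64%, and the 12% to 19% at central values, rest wholly on the assumed SDs and skin response. It would go too far to describe room temperature as known noise that the trial could certainly remove. The firmer part of the case is the adjustment for baseline skin temperature, which needs no assumption about the room and no new measurement.

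**What to change.** - Replace the t-test for skin temperature by a prespecified linear model of post-needling temperature on arm and baseline skin temperature. Report the adjusted arm difference with its 95% confidence interval.
- Log the monitored room temperature for each 10-minute infrared window, and add its change between windows to the model as a covariate.
- Tabulate the room-temperature change by arm. The covariate is measured after allocation, so the adjustment presumes that the arm does not affect the room. The same table would show whether the premise of a constant temperature held.

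The change should be fixed before any unblinded data are seen. It costs one logged value per window (two per participant) and a short passage of analysis text. It also uses one degree of freedom for baseline and one for room change: with 116 participants, the residual degrees of freedom fall from 114 to 112. If the room readings have not been kept, the baseline-adjusted model can still be used alone.

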### Strategies to improve adherence to interventions {11c}

At the beginning of the trial, participants will be informed of the experiment procedure again. They can report their personal feelings at any time during the study, and we will give corresponding feedback as appropriate to increase the interactivity and then improve adherence to interventions.

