#### Clinical evaluation scale for subject sense of acupuncture

This scale is the Chinese version of the Massachusetts General Hospital Acupuncture Sensation Scale (MASS) which has previously been shown to be accurate and reliable [37]. This scale is composed of a main scale and 2 supplementary scales for measuring the spread of the acupuncture sensations and anxiety. At the end of the trial, participants will be asked to fill in the C-MASS form (see additional file 1) to evaluate the intensity of 12 acupuncture sensations on a 0–10-cm VAS, where 0 represents “none” and 10 represents “intolerably strong sensation.” The participants can assess any other sensations by an additional blank row included at the end of the form. The MASS index will then be calculated.

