## Assignment of interventions: blinding

### Who will be blinded {17a}

This is a single-blinded (participants-assessor-blinded) trial. Participants will be asked to wear an eye mask during the whole intervention in an enclosed space. All researchers except the acupuncturists and sonographer will be blind to the group assignment, including statisticians, outcome assessors, and data analysts. We will attempt to validate the successful implementation of the blinding method. All participants will be told that the presence or absence of acupuncture sensation is normal. Furthermore, all researchers will accept training on the RCT specification before the trial and will strictly adhere to the separation principle of each department.

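### The plan lets unblinded staff communicate differently by arm before participants rate their own needling sensations on the C-MASS

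*Protocol article*

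**What the plan says.** Four places in the protocol article bear on this point.

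- **Discussion** (technical problems, sham method): "The acupuncturist and sonologist should be trained several times before the trial begins", partly so that the sham technique is carried out well and partly "to be prepared to give reasonable explanations in case of doubts from sham acupuncture group participants". Only the sham arm is named.
- **Who will be blinded {17a}**: "All researchers except the acupuncturists and sonographer will be blind to the group assignment". The same section sets one message for both arms: "All participants will be told that the presence or absence of acupuncture sensation is normal". It also promises an attempt to verify that blinding worked.
- **Strategies to improve adherence {11c}**: "They can report their personal feelings at any time during the study", and "we will give corresponding feedback as appropriate to increase the interactivity". This covers both arms.
- **Clinical evaluation scale for subject sense of acupuncture**: "At the end of the trial, participants will be asked to fill in the C-MASS form".

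The Discussion also lists, as a limitation, that acupuncturists know which treatment they give. The measure it offers against the resulting suggestion is the eye mask.

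**The concern.** A participant-blinded comparison needs the two arms to differ in the needling and not in what participants are told about it. Here the staff who know the allocation are prepared to speak to one arm in a situation for which the other arm has no stated counterpart. A general invitation to give feedback lets those staff decide what to say. An eye mask does nothing about speech.

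The outcome most exposed is the C-MASS. It is the participant's own rating of sensation, it is a listed secondary outcome, and the objectives describe the arms as with and without *deqi*, so it carries much of the evidence on whether that contrast was achieved. If sham participants are reassured or given reasons in a way that acupuncture participants are not, part of any difference in C-MASS could come from the conversation and not from depth and manipulation. The same talk could influence what participants guess when blinding is checked. Because such an influence would follow allocation, neither randomization nor a larger sample would remove it.

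**Working it through.** No figure in the plan is at issue, so the check sets the provisions side by side.

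1. **Who speaks.** The Discussion names the acupuncturist and the sonologist. Section 17a exempts the acupuncturists and the sonographer from blinding. I take sonologist and sonographer to be the same role. If they are not, the acupuncturist alone still meets both descriptions.

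2. **To whom.** The explanation provision names sham participants. No sentence gives the acupuncture arm an equivalent, and no sentence forbids one. The stated text is asymmetric, but it does not establish that the acupuncture arm hears nothing.

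3. **On what condition.** Explanations follow only if a participant voices doubt. The sham arm gets a superficial needle without manipulation (section 11a, Sham acupuncture group), so doubt there is foreseeable, and the protocol foresees it. How many participants would voice it is not stated. The arm size of 58 is a ceiling, not an estimate.

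4. **What is said.** Section 17a fixes one neutral message for everyone. The Discussion asks only that explanations be reasonable, and section 11c asks only that feedback be suitable. Neither ties the reply to the section 17a message. The reply could repeat that message or go beyond it, and the text allows both.

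5. **When.** Section 11c allows reports and feedback throughout the study, and the C-MASS comes at the end. Feedback given during the session therefore precedes the C-MASS. The timing of the sham explanations is not stated. Nothing holds them back until after the C-MASS.

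6. **Which outcomes.**

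| Outcome | How obtained | Exposure |
|---|---|---|
| C-MASS | Participant's own rating, end of session | Direct: expectation and recall can shift a rating |
| Check of blinding | Method not described in the article | Direct, if participants are asked for a guess after such talk |
| ACF (primary) | Contractions counted over 10 min from recording and playback | Indirect: playback by a blinded assessor protects the reading, though not the participant's state while recorded; the documents do not show that talk changes contractions |

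7. **Size and direction.** The documents give no rate of doubt, no content of the replies and no C-MASS variability. The direction is open too: reassurance might raise sham ratings and narrow the difference, while an explanation that hints at allocation might lower them and widen it.

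Steps 1, 2, 4 and 5 together are enough for the conclusion that, followed as written, the plan permits allocation-dependent replies before a self-reported outcome.

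**The case against.** The strongest reply is that a conditional clause in a Discussion section is being read as a description of conduct. Explanations are given only if doubt arises, their timing is open, and a reasonable explanation may be no more than the common message. That message already answers the most likely sham doubt. Section 17a also plans trial-conduct training for all researchers and a check of blinding. A condensed article need not print staff scripts.

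Much of this stands. It rules out several stronger readings that a reader might infer:

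- *That the arms do receive different communication, or that only the sham arm is given explanations.* The text supports a possibility. It names one arm without excluding the other, and section 11c offers feedback to both, so one cannot say that no acupuncture participant receives any.
- *That staff confirm* deqi *aloud in the acupuncture arm.* Nothing says so. The acupuncturist manipulates the needle to obtain the sensation and records their own perception on a separate scale at the end.
- *That the primary outcome is compromised.* Talk could fall within the ACF recording, but this is not stated, and no effect on contractions is shown.
- *That a sham explanation reveals the allocation.* This is conceivable, but a masked participant would not necessarily know what the other arm is told.

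The objection does not dispose of the point. The concern is not that a script is absent from the article. It is that the article states a provision for one arm, to be carried out by unblinded staff, alongside a general feedback rule that does not limit what they say. The common message reduces the risk, but neither provision is bound to it.

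**Conclusion.** The point holds as a risk of bias that the plan creates and could easily avoid. It mainly concerns the C-MASS and the planned check of blinding. For ACF it is a possibility only. Its size and direction cannot be estimated from the documents, and I attach no number to it.

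The conclusion assumes that the unblinded sonographer is the sonologist of the Discussion (or that the acupuncturist alone suffices), and that no document outside the article already binds replies in both arms to the common message. If such a rule exists, the Discussion and section 11c need only be brought into line with it. The change is worth making but does not put the design in question.

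**What to change.** Reword the Discussion sentence so that the explanation provision applies in identical terms to both arms, and align section 11c with it. From the start of the session until the C-MASS and any blinding question are completed, a comment or doubt about needling sensation, in either arm, gets the neutral section 17a statement in the same words. Fuller answers follow afterwards. Reports of pain, adverse reactions or a wish to stop, and ordinary procedural or comfort questions, are handled as usual and fall outside the rule.

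The cost is two edits and a short item in the training already planned for the acupuncturist and sonologist. The downside is slightly less conversational contact. In-session cooperation still matters, because participants must stay in bed and complete the recordings, and this is why procedural and comfort questions stay open. There is no follow-up whose adherence could suffer.
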